**Methods and analysis:**

Three academic centres in Québec will measure inflammatory biomarkers alongside BDR and/or BPT interpretation for patients with suspected asthma referred by primary care providers (PROPULSION SANTÉ, NCT06981169). Consenting patients aged ≥6 years will undergo FeNO, BEC and BDR testing. If BDR is non-diagnostic, subsequent BPT will be prioritised for patients with ≥1 elevated biomarker (BEC ≥300 /µL, (FeNO ≥25 ppb if ≥12 years or FeNO ≥20 ppb if <12 years)); others will follow usual timelines. Reports to the referring healthcare providers will include standard interpretation of BDR/BPT and biomarker results to state exacerbation risk and suggested corticosteroid dosage. Asthma control and quality of life will be assessed at baseline and remotely at 4, 8 and 12 months. The primary outcome will be the delay from the reception of test request for the diagnosis of asthma patients with versus without elevated biomarker(s). Secondary outcomes include biomarkers’ diagnostic performance, asthma control, quality of life, health benefits, cost-effectiveness, environmental impact and patient satisfaction. We aim to recruit 1500 patients to PROPULSION SANTÉ, with optional biobanking for translational sub-studies for 123 adults (DIVE, NCT05992519) and 123 children (DIVE2, NCT07011394).

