### Setting

The study will be conducted at three Quebec medical centres: CHUS, CHUSJ and MHC-MUHC. A dedicated research respiratory therapist will be assigned to each centre for 1 year to facilitate recruitment through convenience sampling. With participant consent, longitudinal follow-up by email will occur at 4, 8 and 12 months after the initial diagnostic visits.

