For the primary outcome of waiting time differences, the baseline diagnostic delay, prior to the project implementation, will be established based on the time elapsed between the initial request for an asthma diagnostic test made by primary care and the performance of that test. During the intervention, diagnostic delays will be monitored prospectively, both overall and stratified by inflammatory status. We will apply linear mixed-effects models with restricted maximum likelihood estimation. These models will incorporate (high-risk vs low-risk), study period at time of inclusion, and the number of awaiting tests as fixed effects. Random effects will account for within-centre clustering and repeated measurements. In addition, Kaplan-Meier survival curves will be constructed to visualise the probability of remaining undiagnosed over time for both high-risk and low-risk inflammatory phenotypes. These curves will allow for a graphical representation of differences in diagnostic efficiency between groups. Cox proportional hazards regression will be used to identify significant predictors of waiting time with HRs and 95% CIs reported.

Diagnostic performance in the secondary outcome will be evaluated through ROC analysis, calculating the area under the curve (AUC) with 95% CIs for each individual marker and for their combined use. Sensitivity, specificity, positive and negative predictive values and likelihood ratios will be calculated with their respective 95% CIs.

Health utility values will be derived from EQ-5D questionnaires^39 52 53^ completed at baseline and follow-up visits. Quality-adjusted life years will be calculated using the AUC method, connecting utility values across measurement time points. This approach integrates health-related quality of life over the 12-month follow-up period. To assess the financial implications of implementing FeNO testing within the provincial healthcare framework, we will develop a budget impact model for the MSSS. Environmental and satisfaction-related outcomes will be analysed using descriptive statistics. CO₂ emissions from inhalers dispensed to non-asthmatic individuals will be estimated based on Cascades Canada data,^27^ and patient satisfaction with inflammometry will be assessed using structured questionnaires.

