### Discussion

This study addresses a critical gap in the literature by prospectively evaluating the implementation of inflammatory biomarkers in a real-world primary care referral pathway across both adult and paediatric populations. Beyond its scientific contribution, our protocol will optimise clinical resources by reducing the backlog of approximately 3000 respiratory function tests, currently awaiting completion across the three participating centres, through the engagement of study-dedicated respiratory therapists.

We anticipate that this study will demonstrate the utility of inflammatory biomarkers as effective triage and prioritise instruments for BPT. Given the high rate of false positives in respiratory testing as well as the substantial rate of clinical misclassification in Canada (between 33% and 45% in adults and children),^20 22^ our study will calculate optimal biomarker thresholds to achieve 90% specificity, positive predictive value (PPV) exceeding 80% and LR+ greater than 10—parameters essential for reliable diagnostic confirmation.^57^ In effect, this strategy sacrifices sensitivity in favour of specificity, leading to high PPV and LR+.

Existing literature supports the relevance of our approach. Li *et al* conducted a large retrospective cohort study involving 7463 adult patients with suspected asthma in secondary care. Among the 2349 patients with complete biomarker data, concurrent elevation of FeNO (> 40 ppb) and BEC (>0.3×10ˆ9 cells/L) was associated with a diagnostic specificity greater than 95%.^58^ Similarly, Nekoee *et al* demonstrated that combining biomarkers with spirometry improved diagnostic accuracy (AUC 0.82, 95% CI 0.78 to 0.86),^59^ reinforcing the relevance of inflammometry in routine assessment. Additionally, the predictive value of both BEC and FeNO has been demonstrated in adults,^812 15 16 19 60^,^70^ and to a lesser extent in the paediatric^50^ populations, with significant clinical implications for early intervention and treatment adjustment. Furthermore, these biomarkers are valuable tools for therapeutic decision-making, as elevated values are associated with a better response to anti-inflammatory therapies.^71^,^75^ As modifiable indicators, the inflammatory signals provided by BEC and FeNO highlight the importance of early measurement to better prioritise patients requiring timely inflammation control.^15 61 62 64^

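### A fall in diagnostic delay against the pre-project baseline cannot be attributed to biomarker triage, because study-funded therapists arrive at the same time

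*Protocol article*

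**What the plan says.** For the primary outcome, the Statistical methods section first fixes a reference: "the baseline diagnostic delay, prior to the project implementation, will be established based on the time elapsed" from the primary care request to the test. It continues: "During the intervention, diagnostic delays will be monitored prospectively, both overall and stratified by inflammatory status". The mixed model has risk group, study period at inclusion and number of awaiting tests as fixed effects. Kaplan-Meier curves compare the two risk groups.

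The Abstract defines the primary contrast as concurrent: delay in asthma patients with, against without, an elevated biomarker. The Intervention section sets the triage rule. After non-diagnostic spirometry, high-risk patients have bronchial provocation testing (BPT) prioritised to within 2–4 weeks, and low-risk patients stay on the standard list.

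On staffing, the Setting section says: "A dedicated research respiratory therapist will be assigned to each centre for 1 year to facilitate recruitment through convenience sampling". The Discussion names this as an expected benefit of the project: "reducing the backlog of approximately 3000 respiratory function tests, currently awaiting completion across the three participating centres, through the engagement of study-dedicated respiratory therapists".

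**The concern.** The stated aim is to learn whether biomarker prioritisation shortens diagnostic delay. That question needs a usual-care reference.

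The concurrent contrast does not supply one. One group is booked early by rule and the other is not, so a gap is close to guaranteed. The gap also adds any lengthening of low-risk waits to the high-risk gain.

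The pre-project baseline is the only usual-care reference described. The project period differs from it in two ways at once: triage, and a therapist at each centre whom the authors expect to reduce the backlog. No comparison centre, staffing-only period or capacity term is described, and biomarker status is not described for the baseline patients. The limitations in the Discussion do not mention the overlap.

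At stake is how the result is used. A health system that adopted triage without the extra staff could see longer low-risk waits and little or no overall gain.

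**Working it through.** The article gives no figure for the before-after change, so there is none to reproduce. The checks below ask what each comparison can identify.

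**1. Capacity alone (Little's law).** Wait = queue ÷ throughput. From the article: about 3000 tests pending, waits over 1 year. Assumed: throughput of 3000 tests a year (a wait of 12 months), and E extra tests a year. With the queue held at 3000, wait = 12 × 3000 ÷ (3000 + E) months.

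| E per year | Wait (months) | Fall |
|---|---|---|
| 0 | 12.0 | 0% |
| 250 | 11.1 | 7.7% |
| 500 | 10.3 | 14.3% |
| 1000 | 9.0 | 25.0% |
| 1500 | 8.0 | 33.3% |

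These falls occur at a constant queue length, so adjusting for the number of awaiting tests does not remove them.

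**2. When that covariate does help.** Assume instead a 14-month wait, so throughput is 3000 ÷ 14 = 214 a month. If E tests are taken off the backlog and throughput then returns to its old level, wait = (3000 − E) ÷ 214, or 11.7, 9.3 and 7.0 months for E = 500, 1000 and 1500. Here capacity acts only through queue length, which the model includes. If the extra capacity is kept, wait = (3000 − E) ÷ (214 + E/12), or 9.8, 6.7 and 4.4 months. The further drop comes from throughput, which the model does not measure.

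**3. Triage with and without extra capacity.** A queue was simulated under these assumptions: 3000 pending; arrivals and base throughput of 3000 a year; half high-risk; all tests in one queue; extra tests in year 1 only; 730 days, with unfinished waits counted up to day 730. Mean waits in days:

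| Order | Extra tests | All | High-risk | Low-risk |
|---|---|---|---|---|
| Chronological | 0 | 306.3 | 304.3 | 308.4 |
| Chronological | 750 | 261.0 | 259.8 | 262.2 |
| Chronological | 1500 | 215.6 | 215.0 | 216.2 |
| Priority | 0 | 306.3 | 122.2 | 494.1 |
| Priority | 750 | 261.0 | 101.3 | 423.8 |
| Priority | 1500 | 215.6 | 91.0 | 342.7 |

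- Overall mean: triage leaves it unchanged at each capacity. Across this whole closed queue the fall is due to capacity.
- Concurrent gap, no extra capacity: 494.1 − 122.2 = 371.9 days. The high-risk gain is 304.3 − 122.2 = 182.1 and the low-risk loss is 494.1 − 308.4 = 185.7. The gap is about twice the gain.
- High-risk before-after fall with 1500 extra tests: 304.3 − 91.0 = 213.3 days. Crediting capacity first gives it 304.3 − 215.0 = 89.3 days (42%). Crediting triage first leaves capacity 122.2 − 91.0 = 31.2 days (15%). With 750 extra, the fall is 304.3 − 101.3 = 203.0 days and the capacity share is 44.5 (22%) or 20.9 (10%).
- Low-risk loss with 1500 extra tests: before-after it looks like 342.7 − 308.4 = 34.3 days. At equal capacity it is 342.7 − 216.2 = 126.5 days. Added staff can mask the cost of triage.

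**4. Study period.** Triage and staffing start together, so a before/after term is aliased with both. Calendar terms within the project do not separate them either, since no project period is described with one and not the other.

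**The case against.** The strongest reply is that the primary contrast is not before-after. The Abstract, the group term in the model and the Kaplan-Meier curves all compare high- with low-risk patients in the same period, and both groups share the therapists. This stands: added capacity does not create that gap. In the simulation it only changes its size (371.9, 322.5 and 251.7 days at 0, 750 and 1500 extra tests).

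A reader might infer that the plan will credit an overall fall in delay to the biomarkers. The documents do not say so. The Discussion credits backlog reduction to the therapists, the Conclusion speaks of delay in patients with inflammatory phenotypes, and the baseline is only to be established and delays monitored.

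A reader might also infer that re-ordering can never lower a reported mean. That holds only across everyone in a closed queue. If 60% or 70% of confirmed asthma patients were high-risk (assumed), the no-extra-capacity waits give 0.6 × 122.2 + 0.4 × 494.1 = 271 days or 0.7 × 122.2 + 0.3 × 494.1 = 234 days, against 306, with the same slots. The study also enrols a convenience sample of 1500 against about 3000 pending tests, so prioritised participants can overtake non-participants.

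Finally, the therapists' stated role in the Setting section is recruitment, so the throughput they add is unknown. That limits any claim about size. It does not remove the overlap, since the Discussion expects them to cut the backlog.

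**Conclusion.** The point holds for any reading of the primary outcome against usual care. The concurrent contrast is free of the staffing confound, but it largely restates the booking rule and cannot by itself show that delay fell. The one usual-care reference described changes with triage and staffing together. An overall before-after fall, or a high-risk fall against the baseline, could therefore be wrongly taken as a triage effect. Study period is aliased with both changes, and the number of awaiting tests captures queue length but not throughput.

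The size cannot be determined from the documents. The 8% to 33% range for capacity alone and the 10% to 42% capacity share of the high-risk fall rest on assumed throughput, extra tests, a 50% high-risk fraction and a single queue. They show that the effect could matter, not how large it will be.

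**What to change.** - State that the before-after change in delay is descriptive and reflects capacity and triage combined.
- Extract bronchodilator reversibility tests and BPTs completed per centre per month, before and during the project, marking those delivered by study-funded therapists.
- Report the high-risk gain and the low-risk loss separately, not only their difference.
- As a supportive analysis, re-assign the BPT dates completed in each centre in requisition order, and use that schedule as a chronological reference for both groups. State its assumptions on cancellations, internal-referral priority and non-participants in the queue.

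The cost is booking-data extraction, one extra analysis and a narrower headline claim. No new patients, visits or staff are needed.

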Objective testing is essential for accurate asthma diagnosis, especially given high rates of overdiagnosis estimated at 33% in adults and 44% in children in Canada.^20^ Relying on subjective clinical criteria for asthma diagnosis has led to disease overestimation, impacting treatment decisions and healthcare resources.^21^ Spirometry is recommended to demonstrate post-bronchodilator reversibility (BDR), an increase in forced expiratory volume in 1 s (FEV1) ≥200 mL and ≥12% in adults and ≥12% in children and adolescents).^6^ However, spirometry is inconclusive in up to 80% of cases (and over 60% in children), necessitating a methacholine bronchial provocation test (BPT).^22 23^ Furthermore, identifying post-bronchodilator reversibility is of doubtful clinical consequence, as associated with other diseases (eg, chronic obstructive pulmonary disease) and unrelated to the risk of asthma attacks.^24 25^

Methacholine BPT is a relatively cumbersome procedure, requiring monitoring by specialised hospital units and significant testing time, which limits accessibility. These constraints contribute to both over-diagnosis and under-diagnosis, with significant individual, societal, environmental and economic consequences.^1421 26^,^28^

Inadequate access to objective tools in primary care delays or impairs treatment, worsening asthma control, quality of life and healthcare costs.^6 21^ Zafari *et al* estimated that improved diagnostic algorithms reducing sub-optimal asthma control by 10% could save $50.5 billion over 20 years in Canada.^4^

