### Intervention

The interpretation of respiratory function tests and biomarkers will be performed by the principal investigator pulmonologist at each centre or by trained designated collaborating pulmonologists by following these models:

High-risk inflammatory asthma is defined by FeNO ≥25 ppb or BEC ≥300 cells/µL in participants ≥12 years (≥20 ppb or ≥300 cells/µL in children aged 6 to <12 years)^15 50^ : one or more elevated biomarkers will be interpreted as a high risk of asthma exacerbation. If spirometry is non-diagnostic, BPT will be prioritised (<2–4 weeks).Low risk inflammatory asthma is defined by FeNO <25 ppb and BEC <300 cells/µL (<20 ppb or <300 cells/µL in children aged 6–<12 years)^15 50^: this will be interpreted as a low risk of asthma exacerbation. If spirometry is non-diagnostic, BPT will be scheduled according to the standard waiting list.

Results of biomarkers will be integrated on the medical report indicating the probability (high/low) of asthma exacerbation and suggested management with either ICS taken as-needed (T2-low) or regularly (T2-High) ICS if clinically appropriate, which will be forwarded to the referring physician.

The patient test pathway based on their respiratory test and the results of the inflammometry assessment is summarised in figure 2.

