### Outcomes measures

#### Primary Outcome

The primary outcome, diagnostic delay, will be defined as the interval between primary care requisition for pulmonary function testing and the last confirmatory diagnostic test conducted (BDR or BPT). This continuous outcome will be analysed longitudinally and stratified by biomarker-guided diagnostic strategies, also adjusting for the time of inclusion in the study. Sensitivity analyses will also examine diagnostic delay for FeNO and blood eosinophils considered separately.

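### The pre-implementation baseline delay stops at the requested test, but the study's diagnostic delay stops at the last confirmatory test, so comparing the two is biased against the study period

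*Protocol article*

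**What the plan says.** The Primary Outcome section of the protocol article defines diagnostic delay as "the interval between primary care requisition for pulmonary function testing and the last confirmatory diagnostic test conducted (BDR or BPT"). The abstract (Methods and analysis) gives the primary comparison as "the delay from the reception of test request for the diagnosis of asthma patients with versus without elevated biomarker(s").

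The Statistical methods section, for the same primary outcome, then sets up a baseline delay from before the project. It is measured as "the time elapsed between the initial request for an asthma diagnostic test made by primary care and the performance of that test". The section continues: "During the intervention, diagnostic delays will be monitored prospectively, both overall and stratified by inflammatory status". The mixed model has risk group, study period at inclusion and the number of tests awaiting as fixed effects. The text does not say whether pre-implementation records are among the data modelled.

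Three other places bear on the point. The Introduction says that "spirometry is inconclusive in up to 80% of cases", with a figure above 60% in children. The Intervention section says of high-risk patients: "If spirometry is non-diagnostic, BPT will be prioritised (<2–4 weeks"); low-risk patients keep the ordinary queue. The Discussion expects the backlog to fall "through the engagement of study-dedicated respiratory therapists".

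**The concern.** The two definitions end at different events. Take a patient referred for BDR whose result is non-diagnostic. Before the project, the clock as written stops at the BDR. In the study it runs on to the BPT. The baseline therefore leaves out the interval that biomarker prioritisation is meant to shorten, and no section aligns the two definitions.

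This matters because the abstract asks whether prioritisation reduces diagnostic delay. The concurrent high-risk versus low-risk contrast puts both groups on one clock, but part of the difference is fixed in advance: one group is booked within weeks and the other waits in the ordinary queue. If capacity is limited, moving some patients forward may move others back. A gap between the groups could then appear with no fall in average delay. The baseline is the only pre-prioritisation reference that the article describes, so it should measure the same quantity as the outcome.

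**Working it through.** The protocol gives no numerical baseline delay to reproduce. Its sample-size figure (Cohen's f of 0.07) does not bear on this point.

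**Inputs from the protocol**
- q, share of BDR tests that are non-diagnostic: 0.8 as an upper figure, and above 0.6 in children (Introduction).
- P, prioritised BPT wait: 2 to 4 weeks (Intervention).
- Waits before the project exceed one year (Introduction), without a split between first test and BPT.
- Some patients are referred directly for BPT (Figure 2 legend); their share is not given.

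**Assumptions**
- W1, wait for the first test: 52 weeks before the study; W1′ is its value during the study.
- W2, usual wait from BDR to BPT: 26 or 52 weeks, unchanged for low-risk patients unless stated.
- b, share referred for BDR first: 0 to 1.
- h, share high-risk: 0.5.

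**Formulas (expected delay in weeks)**
- Baseline as written: W1
- Baseline on the outcome's clock: W1 + b·q·W2
- Study, high-risk: W1′ + b·q·P
- Study, low-risk: W1′ + b·q·W2
- Study, all: W1′ + b·q·(h·P + (1−h)·W2)
- Clock gap: b·q·W2

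**Base case** (b = 1, q = 0.8, W1 = W1′ = W2 = 52, P = 4)
- Baseline as written: 52.0. On the outcome's clock: 52 + 0.8 × 52 = 93.6. Gap: 41.6.
- High-risk: 52 + 0.8 × 4 = 55.2. Change from baseline: +3.2 as written, −38.4 on one clock.
- All: 52 + 0.8 × 28 = 74.4. Change from baseline: +22.4 as written, −19.2 on one clock.
- High-risk minus low-risk: 55.2 − 93.6 = −38.4, whichever baseline is used.

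**Variations** (change from baseline: as written / on one clock)

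| W1→W1′ | b | q | W2 | P | Gap | High-risk | All |
|---|---|---|---|---|---|---|---|
| 52→52 | 1 | 0.8 | 26 | 4 | 20.8 | +3.2 / −17.6 | +12.0 / −8.8 |
| 52→52 | 1 | 0.6 | 26 | 2 | 15.6 | +1.2 / −14.4 | +8.4 / −7.2 |
| 52→40 | 1 | 0.8 | 52 | 4 | 41.6 | −8.8 / −50.4 | +10.4 / −31.2 |
| 52→52 | 0.5 | 0.8 | 52 | 4 | 20.8 | +1.6 / −19.2 | +11.2 / −9.6 |
| 52→52 | 0.5 | 0.6 | 52 | 4 | 15.6 | +1.2 / −14.4 | +8.4 / −7.2 |
| 52→52 | 0 | any | any | any | 0 | 0 / 0 | 0 / 0 |

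With b = 1 and W1 unchanged, over q = 0.6 to 0.8, P = 2 to 4 and W2 = 26 to 52, the high-risk change is +1.2 to +3.2 weeks as written and −13.2 to −40.0 on one clock. With h = 0.4 or 0.6 in the base case, the change for all participants is +26.2 or +18.6 as written, and −15.4 or −23.0 on one clock.

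**When the sign does not reverse.** The apparent change turns negative once the first-test wait falls by more than b·q·P for high-risk patients (3.2 weeks in the base case), or by more than b·q·(h·P + (1−h)·W2) for all participants (22.4 weeks in the base case, 8.4 with b = 0.5 and q = 0.6).

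**Displacement.** Suppose BPT capacity is fixed, so that the mean BPT wait stays at 52 weeks. Then 0.5 × 4 + 0.5 × x = 52 gives a low-risk BPT wait of x = 100. High-risk minus low-risk becomes 0.8 × (4 − 100) = −76.8 weeks, while the change for all participants on one clock is 0. This is an extreme case. It shows only that the concurrent contrast does not measure net change.

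**The case against.** - **The declared primary comparison is sound on this point.** It is high-risk versus low-risk within the study, both on the same clock, and the article specifies no before-after test. This stands. A reader might infer that the clock mismatch invalidates the primary contrast or reduces it to a check that the schedule was followed. The documents do not support that. The contrast's limits come from the scheduling rule and are a separate design question.
- **A matched baseline would not isolate prioritisation either.** Study-funded therapists also clear the backlog. This stands too, so the baseline should not be called the one comparison that settles the effect of prioritisation.
- **The wording may only be loose.** The baseline is itself called a diagnostic delay, and Study visits describes spirometry followed, if negative, by methacholine as one procedure. That is possible, but the literal reading is the more natural one, and an analyst extracting dates would follow it.
- **Sign reversal depends on chosen inputs.** The 80% is an upper figure, the split of waits is unknown, direct BPT referrals have no gap, and extra staff may shorten the first-test wait. A reader might infer that the comparison must reverse; the documents do not show that. The direction of the bias does not depend on these inputs, since the baseline clock as written is never the longer one.
- **Some of the remedy is already planned.** Delays are monitored overall and by risk group, and the model carries study period and queue length. These help, but they do not correct a baseline that ends at the wrong event.

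**Conclusion.** The point holds as an inconsistency in how one quantity is defined in two sections. As written, any comparison of study-period delay with baseline is biased against the study period by b·q·W2. With everyone starting at BDR, that is 15.6 weeks at q = 0.6 and a 26-week BPT wait, and 41.6 weeks at q = 0.8 and a 52-week BPT wait. It shrinks in proportion to the share referred directly for BPT and is zero if all are. The sign can reverse when the first-test wait changes little. The sizes rest on assumed waits and referral mix, which the article does not give.

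The high-risk versus low-risk estimate is numerically unaffected. On its own it cannot show a net reduction in delay, because the scheduling rule creates the gap and low-risk patients may be displaced. The mismatch should be removed before baseline data are extracted.

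**What to change.** 1. In Statistical methods, define the baseline delay exactly as in Primary Outcome: from requisition to the last confirmatory test, whether that is BDR or BPT. Report it by centre and by the test first requested.
2. State whether pre-implementation records enter the mixed model and, if so, how the study-period term codes them.
3. Compare the overall and low-risk study-period delays, which are already to be monitored, with that baseline. The low-risk comparison is the one that would reveal displacement.
4. State that the change from baseline will not be attributed wholly to biomarkers, because the study's therapists also add capacity.

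The high-risk versus low-risk contrast can remain the declared primary comparison.

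The cost is a change of wording and one further test date per baseline record; the article does not name the source of those records. The before-after comparison will remain confounded by capacity even when both periods use one clock.
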